Red blood cell (RBC) transfusions have been associated with a higher incidence of ROP, and its severity is directly related to the volume of blood transfused (11). In term newborns, fetal hemoglobin makes up about 60%–80% of total hemoglobin. In ELGANS, fetal hemoglobin makes up 90%–95% of total hemoglobin (12). Although the physio-pathological mechanism is unknown, it is postulated to be linked to the significant increase in adult hemoglobin (HbA) levels. HbA releases up to 50% more oxygen than fetal hemoglobin (HbF) to peripheral tissues. Because blood from bank donors comes exclusively from adults, RBC transfusions increase HbA levels generating a hyperoxic stimulus in the retinal capillaries that could trigger the development of ROP (13–15). Moreover, low HbF levels have also been associated with ROP (16, 17). Additionally, recent studies have suggested that HbF could protect against oxidative stress due to its biochemical properties (18, 19).

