Based on these premises, the utilization of umbilical cord blood transfusion (UCB) from healthy newborns has been proposed to prevent ROP in preterm infants (6). This approach is feasible and safe, although it is not exempted from the inherent risks associated with allogeneic transfusions (20). As an alternative, autologous UCB transfusion is suggested for treating anemia in ELGANs. Autologous UCB transfusions (UCBa) have been widely employed in full-term infants with congenital heart diseases requiring extracorporeal surgery (21, 22). The safety of UCBa has been extensively demonstrated, with no adverse effects reported in numerous studies involving over a hundred transfused patients (23–26). Furthermore, the transfusion risks associated with using allogeneic blood are eliminated in this approach. In premature patients, less information is available. However, most studies have shown that a volume ranging from 20 to 25 ml/kg is usually collected, meeting the requirements for at least one to two autologous transfusions (24, 25). Not only has UCBa been seen as equivalent to adult-donor RBC in increasing hematocrit (24), but this approach could also sustain HbF levels during the critical period of extremely preterm infants’ development. Additionally, UCB is enriched with self-hematopoietic growth factors, hematopoietic stem cells, and mesenchymal stem cells, which play a crucial role in developing connective tissue and blood vessels (27). Some authors have hypothesized that these cells could modulate angiogenesis and promote an appropriate retinal microenvironment, potentially reducing the progression of ROP (27–29).

We hypothesize that using UCBa in the first weeks after birth will contribute to keeping elevated HbF blood concentrations and subsequently reduce the risks inherent to HbA of interfering with the growth of the retinal vascular system.

This study aims to assess the effect of UCBa transfusion vs. standard treatment with packed adult-donor RBC in the incidence of ROP. Secondary objectives are to determine the impact of UCB autologous transfusion on the expression of biochemical markers of ROP, to determine the effect of UCB autologous transfusion on oxidative stress, to characterize the specific composition of stem cells in UCB in preterm newborns and its relationship with complications of prematurity.

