### Intervention

Patients will be randomized to receive either whole UCBa, intervention group, or standard adult-donor packed RBC, control group. For patients with anemia requiring blood transfusion according to the Spanish Society of Neonatology's standards Committee threshold's recommendations (30), the responsible physician will make the corresponding request for transfusion indicating the volume needed. The Blook Bank will supply UCBa or RBC according to the patient's group, but bag labeling will be indistinguishable. In case there is not enough UCBa, RBC will be administered. As the maximum storage of UCB is 35 days, both groups will receive adult-donor RBC concentrates after this age. Transfusion's traceability will always be maintained through the e-Delphyn Transfusion Service software. UCB extraction and storage protocols are detailed in Appendix I.

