### Statistical analysis

The following sets of analyses are planned: (1) All included patients, regardless of whether they were transfused or not; (2) All included patients who received transfusions, as per intention-to-treat (including intervention group patients who received adult donor blood transfusions due to unavailability of umbilical cord blood); (3) All included patients who received transfusions as per protocol (excluding intervention group patients who received adult donor blood transfusions). Secondary analyses will also examine the effect of the two treatment strategies on the described secondary variables. An interim analysis of the results will be conducted once half of the sample has been collected to assess the presence of any relevant safety or mortality outcomes. An external committee will be proposed to perform the calculations while maintaining blinding until evaluation.

Categorical variables are described with each category's numerical count (percentage). If the application assumptions are met, they are compared with Pearson's chi-square test, and if not, Fisher's exact test. Continuous variables are represented with Tuckey box plots. If the constant variables are standard (*p* > 0.05 in the Shapiro–Wilk test), they are described with the mean ± standard deviation. They are compared using Student's *t*-test, first testing the hypothesis of equality of variances using Levene's test. If abnormal, they are described with a median (p25, p75) and compared with the nonparametric Mann–Whitney *U*-test. Comparison between both groups of repeated measures over time is performed by a two-way analysis of variance (ANOVA) test, first testing Mauchly's sphericity hypothesis and rejecting it with *p* < 0.05. Survival times are expressed with their median [95% confidence interval (95% CI)], and between-group comparison is performed with the log-rank test. Throughout the study, a *p* < 0.05 is accepted as the limit of statistical significance. The magnitude of the effect is quantified with the risk difference (expressed as a percentage), and its precision is indicated with the 95% CI.

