The limitations of this study are inherent to a clinical trial and are mainly manifested in two aspects. Firstly, the difficulty of recruiting patients in the complex environment of Neonatal Intensive Care Units at the birth of a preterm patient, where uncertainty about potential complications of this condition and other concurrent factors makes it challenging to approach the parents of eligible patients. For this reason, a multicenter design has been implemented, including three clinical units with sufficient annual admissions. On the other hand, there might be cases where the volume of blood collected needs to meet the complete transfusion needs of the patient. It is assumed that the most significant benefit of autologous transfusion will occur within the first two weeks of life due to the pathophysiology of the disease, during which time transfusion needs will be met. However, allogeneic transfusions are usually required as a supplement to meet complete requirements. This hypothesis is reinforced by the results presented by Hellstrom et al. (18), who found that only the drop in HbF during the first week of life was related to ROP. Moreover, the statistical analysis is designed in analysis sets to assess the actual impact of this effect. On the other hand, improving the collection technique and experience could help improve these results. Our group is working on developing an optimized system for cord blood collection.

The relevance of the trial is based on the need to address ROP, a serious ocular complication that currently lacks an effective treatment. Clinical trials like the one presented can be the beginning of a paradigm shift in transfusion medicine, using neonatal blood for neonatal patients whose situation differs significantly from adult patients, thereby improving the quality of care and clinical outcomes in this patient population.

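### The per-protocol set drops, from the intervention arm only, infants given adult blood that the protocol itself prescribes, so it is a biased comparison even if cord blood has no effect

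*Protocol article*

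**What the plan says.** The Statistical analysis section of the protocol article plans three sets:

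- Set 1: everyone included, transfused or not.
- Set 2: transfused infants as randomised, "including intervention group patients who received adult donor blood transfusions due to unavailability of umbilical cord blood".
- Set 3: "All included patients who received transfusions as per protocol (excluding intervention group patients who received adult donor blood transfusions". No exclusion is named for the control arm.

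The Intervention section prescribes adult blood in the intervention arm in two situations. On shortage: "In case there is not enough UCBa, RBC will be administered". Once the 35-day storage limit of cord blood has passed: "both groups will receive adult-donor RBC concentrates after this age".

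Other sections bear on who is excluded. The Introduction describes the usual collection as "meeting the requirements for at least one to two autologous transfusions". The Discussion says that "allogeneic transfusions are usually required as a supplement to meet complete requirements". The Introduction also associates transfusion with a higher incidence of ROP and says "its severity is directly related to the volume of blood transfused". On incomplete cord supply, the Discussion relies on the sets: "the statistical analysis is designed in analysis sets to assess the actual impact of this effect".

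**The concern.** A per-protocol set should remove departures from the protocol. This one removes intervention infants who were treated as the Intervention section directs, and does so in one arm only.

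Whether an intervention infant needs adult blood depends on how many transfusions the infant turns out to need and how much cord blood was banked. Infants with low need or a large banked volume stay; those with high need go. Control infants with equally high need all stay. If need predicts outcome, the two groups differ in prognosis before any effect of the blood product.

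Set 3 is the only set that removes adult-blood recipients, so a reader would naturally take it as the answer to what cord blood does when supply suffices. It cannot answer that, because the contrast mixes product with transfusion need.

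**Working it through.** **The rules side by side.** Three intervention infants follow the protocol: one whose cord blood covers every transfusion, one whose cord blood runs out and who then gets adult blood, and one who is still transfused after day 35. Set 3, read literally, keeps the first and drops the other two. Their control counterparts, with the same needs, are all kept.

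**Inputs.** The plan gives no figure for set 3, so there is none to reproduce. From the document: 41% for death or ROP, 122 infants before dropout (61 per arm), 67 per arm recruited, and cord supply for at least one to two transfusions. The rate of ROP alone at the centre is not given, so 41% stands in for it. Assumed: transfusion counts, the link between need and outcome, and the share of infants kept.

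**Simple calculation, no treatment effect.** Let a fraction f of intervention infants need no adult blood, and let the others have RR times their risk. With 41% overall, the risk among those kept is 0.41 / (f + (1 − f) × RR), compared with 41% in all controls.

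- RR 1, any f: 0.41 / 1 = 41%; difference 0.
- RR 1.5, f 0.5: 0.41 / 1.25 = 32.8%; difference −8.2 points.
- RR 2, f 0.5: 0.41 / 1.5 = 27.3%; difference −13.7 points.
- RR 2, f 0.3: 0.41 / 1.7 = 24.1%; difference −16.9 points.

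With 61 controls and 61 × f kept, the chance of two-sided p<0.05 favouring cord blood is about 11% in the RR 1.5 case and 24% in both RR 2 cases, against a nominal 2.5%.

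**Simulation, no treatment effect.** 67 per arm; negative binomial transfusion counts (k = 2); logistic risk rising with each transfusion, calibrated to 41% overall. Intervention infants are kept if transfused no more often than cord supply allows; all transfused controls are kept.

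| Mean count | Supply | Odds ratio per transfusion | Risk difference (points) | Two-sided p<0.05 | Transfused intervention infants kept |
|---|---|---|---|---|---|
| 3.5 | 2 | 1.11 | −6 to −7 | 8% | 38% |
| 3.5 | 2 | 1.22 | −12 | 15–16% | 38% |
| 3.5 | 2 | 1.35 | −17 | 28% | 38% |
| 3.5 | 1 | 1.35 | −20 | 22% | 19% |
| 3.5 | 3 | 1.35 | −14 | 24–26% | 54% |
| 2 | 2 | 1.22 | −6 | 8% | 58% |
| 2 | 3 | 1.11 | −2 | 6% | 75% |

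Ranges show the spread between repeat runs. The last row combines the mildest assumptions and shows how small the bias can become. With need unrelated to outcome, the difference is 0. Set 2, and the same restriction applied to both arms, give a difference of about 0 and about 5% rejection. The asymmetry is therefore the cause.

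**Death or ROP.** An intervention infant who dies early, after cord blood only, never reaches adult blood and stays in set 3 as an event. Take mean 3.5 and supply 2, and let part of the 41% be deaths after at most two transfusions (an assumed and extreme timing). With early deaths of 5%, 10% and 15%, the difference becomes about −6, 0 and +4 points at odds ratio 1.22, and about −10, −4.5 and +1 at 1.35.

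**The case against.** The strongest counter-argument concerns direction. A reader might infer that set 3 always favours cord blood and will give the most favourable of the three results. The document does not support that. The Primary outcome section names ROP, but the sample size section treats death or ROP as primary because death competes with ROP. For that composite, retained early deaths can cancel or reverse the bias, and neither the death rate nor its timing is given. This objection stands.

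Size is also open: every input except part of the supply figure is assumed, and mild inputs give little bias. This stands too. So does a point of wording. The Introduction links ROP to transfusion and transfused volume and postulates adult haemoglobin as the mechanism; it does not say that the infants needing most blood are the sickest. That need predicts outcome regardless of product is plausible, but it is an inference.

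The day-35 part can be read more narrowly. Set 2 speaks of adult blood given because cord blood was unavailable, and set 3 may mean the same infants. Fewer would then be dropped, but still from one arm only.

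Finally, sets 1 and 2 keep these infants, and set 3 is not named primary. That limits the damage. It does not remove it, because the Discussion leans on the sets to judge the effect of incomplete supply, and the section applies p<0.05 throughout.

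**Conclusion.** The definition is wrong as written: it labels compliant infants as outside the protocol and conditions one arm on a post-randomisation variable. This follows from the text and needs no assumption. A non-zero bias requires only that need be related to outcome.

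For ROP alone, with need prognostic, the bias favours cord blood. Its illustrative size is about −6 to −20 points with 8–28% rejection, and nearer zero when the mildest assumptions are combined. For death or ROP, its direction cannot be stated in advance.

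The point concerns one of three sets. A reader might infer that the trial's main conclusion is compromised; that would follow only if set 3 were taken as evidence of efficacy. The set should be redefined before unblinding.

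**What to change.** 1. Define the per-protocol set by adherence to the assigned strategy in both arms. Count adult blood given under the shortage or 35-day rule as adherent. Exclude only product-dispensing errors, in either arm.
2. If a set with adequate cord supply is wanted, restrict both arms by the same pre-set, objective criterion: banked mL/kg and quality-control result. Record it for every infant before the first transfusion and apply it without regard to allocation. This matters because randomisation takes place just before birth and the Blood Bank holds the treatment list, so its quality acceptance is not automatically blind to arm.
3. Report any comparison limited to infants who received cord blood only as exploratory, not as evidence of efficacy.

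The cost is mostly wording. The revised set no longer isolates infants who received only cord blood, so it answers a different question. Banked volume and quality results must also be recorded for controls; the description of Blood Bank processing is not restricted by arm, but the document does not state that these data will be kept for controls.

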### Primary outcome

The primary outcome is the incidence of ROP in both groups. Diagnosis and staging of ROP will be established according to “International Classification of the Retinopathy of Prematurity, Third Edition (ICROP3)”. ROP diagnosis will be made by an expert ophthalmologist using indirect ophthalmoscopy and RetCam imaging.

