### Secondary outcomes

Outcomes related to effectiveness
-Recovery of hematocrit and hemoglobin values.-Transfusion requirements during admission (number and volume of transfusions received).-Treatment with EPO and other adjuvant treatments for anemia such as iron and folic acid supplementation (time of initiation, number of doses received).-Assessment of post-transfusion tissue oxygen transfer status: Brain and somatic NIRS value, oxygen saturation measured by pulse oximetry, lactate, HbF levels.Outcomes related to safety
-Incidence of acute transfusion reactions.-Incidence of late complications: bronchopulmonary dysplasia, periventricular leukomalacia, necrotizing enterocolitis, hemodynamically significant patent ductus arteriosus, sepsis, and death.Outcomes related to retinopathy markers
-Serum levels of EPO, VEGF and IGF-1.-HbF levels.Outcomes related to ROP treatment
-ROP severity-Laser therapy-Anti-VEGF administrationOutcomes related to UCB cellularity and oxidative stress.
-Quantification of reactive oxygen species in urine.-Composition of stem cells in UCB.

Data concerning retinopathy and oxidative stress biomarkers quantification and stem cells typification is provided in Appendix II.

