### Sample size calculation and power

We consider the development of ROP a competitive outcome with mortality due to its late onset during postnatal development. The combined variable death or ROP was considered the primary study variable. The incidence of death or ROP in our center in ≤28 weeks is 41%. A 50% reduction in the incidence will be considered clinically significant, so considering a significance level of 0.05 and a power of 0.8, the calculated sample size is 122 patients. Assuming a drop ratio of 10%, 134 patients will be recruited for the study (67 in each group).

University and Polytechnic Hospital La Fe is a tertiary center with 6,000–6,500 births annually. In addition, two other recruiting centers, University Clinical Hospital of Santiago (2,000–2,200 births annually) and Maternal and Child University Hospital Complex of Las Palmas (4,500–4,800 births annually), are included in the study, so we estimate that the sample size could be accomplished in the three years of the study duration.

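### The only stated test for categorical variables ignores order, which would cost power for ROP severity if it is analysed as ICROP3 stages

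*Protocol article*

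**What the plan says.** The Statistical analysis section of the protocol article assigns tests by type of variable. For categorical variables: "If the application assumptions are met, they are compared with" Pearson's chi-square test, and otherwise with Fisher's exact test. For continuous variables that fail the Shapiro–Wilk check: "If abnormal, they are described with a median (p25, p75) and compared with the nonparametric Mann–Whitney" test. No trend, rank or ordinal method is named for ordered categories. The one effect measure is the risk difference with a 95% CI.

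Under Secondary outcomes, severity stands beside two treatment items ("ROP severity-Laser therapy", then anti-VEGF use), with no coding given. Under Primary outcome, "Diagnosis and staging of ROP will be established according to" ICROP3, which is an ordered scale.

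The main endpoint is binary in both places where it is described: "The primary outcome is the incidence of ROP in both groups" under Primary outcome, and "The combined variable death or ROP was considered the primary study variable" under Sample size calculation and power. No effect size or power is stated for severity.

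**The concern.** Pearson's and Fisher's tests return the same p-value however the columns of the table are shuffled. Applied to no ROP, stage 1, stage 2 and so on, they treat a move from no disease to the highest stage like a move between two adjacent stages. The evidence for a consistent downward shift is spread over several degrees of freedom, and the test itself carries no direction. A single risk difference does not summarise a multi-level ordered outcome either, so the stated rule gives staged severity no overall directional estimate.

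At stake is the efficiency of one secondary comparison, the one that asks whether disease is milder as well as less frequent. This is a challenge to a rule that the article prints, not to detail left for an analysis plan.

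**Working it through.** **The plan's own figure.** None exists for severity. The stated total of 122 evaluable infants concerns a binary variable, 41% against 20.5%. A two-proportion formula without continuity correction gives 62 per arm (124) at one-sided 0.05 and 79 per arm (158) at two-sided 0.05. So 122 is close to the one-sided value; the sidedness is not stated, and that is separate from this point. The checks below use 122/2 = 61 per arm and two-sided 0.05.

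**Inputs from the article.** 41% affected in controls (this is the rate of death or ROP, used here as a stand-in for ROP) and a 50% reduction, to 20.5%. Odds ratio = (0.205/0.795)/(0.41/0.59) = 0.371.

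**Assumed control distributions (none, then rising severity).**
- 3 levels: 59, 26, 15%
- 4 levels: 59, 13, 14, 14%
- 5 levels: 59, 12, 14, 13, 2%
- 6 levels: 59, 12, 14, 12, 2, 1%

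**Treated distribution.** The odds ratio 0.371 is applied to every cumulative split. For 5 levels this gives 79.5, 7.34, 7.02, 5.39 and 0.75%.

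**Why the loss grows with the number of levels.** The Pearson noncentrality with n per arm is n × Σ(pC − pT)²/(pC + pT).
- 3 levels: 61 × (0.0303 + 0.0336 + 0.0371) = 61 × 0.101 = 6.2, on 2 df (critical value 5.99): power 0.60.
- 5 levels: 61 × (0.0303 + 0.0112 + 0.0232 + 0.0315 + 0.0057) = 61 × 0.102 = 6.2, on 4 df (critical value 9.49): power 0.49.

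The signal is almost unchanged while the degrees of freedom rise. The rank test has nearly the same noncentrality, about 6.2, on 1 df: power = P(Z > 1.96 − √6.2) = P(Z > −0.53) = 0.70.

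**Simulated power** (40,000 trials per row for Pearson against Mann–Whitney; 3,000 for exact Fisher, each with its own Mann–Whitney comparison). Relative loss = 1 − ratio of powers.

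| Levels | Pearson | Rank test | Loss | Fisher | Rank test | Loss |
|---|---|---|---|---|---|---|
| 3 | 0.60 | 0.71 | 15% | 0.58 | 0.70 | 17% |
| 4 | 0.53 | 0.71 | 25% | 0.54 | 0.71 | 24% |
| 5 | 0.48 | 0.72 | 33% | 0.52 | 0.71 | 27% |
| 6 | 0.45 | 0.71 | 37% | not run | – | – |

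**Which branch of the rule applies.** Take a second assumed 5-level distribution, 59, 12, 12, 9, 8%. Expected counts per arm are 61 × (pC + pT)/2 = 42.2, 5.9, 5.5, 3.9 and 3.4, so four of ten cells lie below 5. If Pearson is allowed only when at most 20% of cells are below 5, about 82% of simulated trials go to Fisher. With five levels the Fisher column is therefore the more relevant one.

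**Sensitivity.**
- Weaker effects (odds ratio 0.5 to 0.7): Pearson loses about 21–23% with 3 levels and 43–53% with 5 or 6.
- 64% affected, 5 levels, every stage halved: 10%.
- Severe-to-mild shift at essentially unchanged incidence (for example controls 59, 13, 14, 14% against 59, 27, 10, 4%): Pearson 0.58, rank test 0.11. A 5-level version gives 0.58 against 0.14. The advantage reverses.

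**The case against.** The strongest reply is that the article never says severity will be analysed as stages. It sits beside laser and anti-VEGF use, and the only effect measure suits a yes/no outcome. If severity means severe ROP yes or no, chi-square or Fisher is the usual test and nothing is lost. That stands, and it makes the point conditional.

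The tests named are also valid; they hold the 5% error rate. In the scenarios used here most of the signal is none against any ROP, and a simple binary test of that contrast has power 0.69 against about 0.71 for the rank test. The rank test therefore recovers what Pearson loses but adds little to the binary comparison. That stands too.

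A reader might infer four stronger things that the article does not support.
- *The plan loses a third of its power.* That is one cell of the table (five levels, Pearson), on an assumed stage distribution.
- *A rank test has no drawback.* The severe-to-mild scenario shows that it does. The trial's hypothesis and planned effect do, however, concern less ROP overall, the pattern in which a rank test gains.
- *A significant result would leave the worse arm unknown.* The test has no direction, but the plan also reports counts and percentages per category.
- *Death must be ranked as the worst category.* The article treats death as competing with ROP when sizing the trial, but lists it separately under safety. Folding it into severity would change what is being estimated, and the ordering problem does not require it.

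An unseen analysis plan might name an ordinal method, but it would then depart from the rule printed here.

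**Conclusion.** The point holds in a limited form. As written, the only rule for categorical variables ignores order, and the rank test is kept for continuous data. If ROP severity is analysed as ordered ICROP3 stages and the effect runs in one direction across them, the relative power loss at the planned effect is about 15–37% with Pearson (3 to 6 levels) and about 17–27% with Fisher (3 to 5 levels). Other plausible one-directional scenarios run from about 10% to about 50%. All of this rests on assumed stage distributions, a 41% affected rate borrowed from death or ROP, and 61 infants per arm.

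This is an optional efficiency improvement for one secondary outcome with no stated power. It does not touch the validity of the tests, the binary primary endpoint or the sample size.

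**What to change.** In the Statistical analysis section, state that ROP severity is the worst ICROP3 stage reached per infant, ordered, with no ROP as the lowest level. Compare it with a Mann–Whitney test or a proportional-odds model, and report a directional effect estimate with its 95% CI (for example the common odds ratio). Keep the per-stage counts by arm. Keep chi-square or Fisher for binary and unordered variables. If the intention is a yes/no severity outcome, say so and give the cut-off; the present rule then suffices.

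The cost is a few sentences and no new data, and the change can be made before the blind is opened for analysis. The drawback is low power for a shift confined to infants who have ROP. The per-stage counts and the separate laser and anti-VEGF outcomes cover that in part.
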